## 4. STUDY DESIGN

### 4.1. Overall Design

This is an open-label, multi-center Phase 1 study in adult participants to evaluate safety, tolerability, PK, and PD of PF-07248144 in locally advanced or metastatic selected solid tumors (ER+HER2- breast cancer, CRPC, or NSCLC) and early signs of clinical activity of PF-07248144 as a single agent and in combination in ER+HER2- breast cancer. The overall study design is depicted in the schema ([Section 1.2](#)).

**Part 1** dose escalation consists of: Part 1A, Part 1B [REDACTED]

**Part 1A** contains dose escalation as monotherapy in participants with locally advanced or metastatic ER+HER2- breast cancer, CRPC, or NSCLC that are resistant or intolerant to standard therapy or for whom no standard therapy is available, to determine the MTD and select the RDE. Participants will receive escalating doses of PF-07248144. BLRM guided by EWOC principle will be used to guide dose escalation process and determine the MTD. [REDACTED] Maximum allowable PF-07248144 dose increment is 100% unless in circumstance defined in [Section 4.3.3](#). DLT will be assessed during Cycle 1 (the first 28 days with the inclusion of C2D1 laboratory assessments). Each dose level group will be approximately 3 participants, with at least 1 DLT-evaluable participant per cohort in the first 2 cohorts and at least 2 DLT evaluable participants per dose level group in the remaining cohorts for Part 1A. Per BLRM design, expanding additional

participants at lower dose levels is allowed to assess safety. Additional dosing frequency such as intermittent dosing may be considered if supported by emerging clinical data.

**In Part 1B**, PF-07248144 in combination with fulvestrant, will be evaluated for dose finding in participants with locally advanced or metastatic ER+HER2- breast cancer (2L+) who have progressed after at least 1 line of treatment with an endocrine therapy and CDK4/6 inhibitor to determine the MTD and RDE for this combination. The definitions of RDE and RP2D are provided in [Section 4.3.7](#). Combination RDE may be different from monotherapy RDE due to potential toxicity overlap or drug-drug interaction.

[REDACTED]

[REDACTED]

[REDACTED] Treatment will continue until PD, unacceptable toxicity, or participant refusal, whichever occurs first.

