BLRM specifically developed for double and triple combinations will be used for dose finding in Part 1B, [REDACTED] PF-07248144 may start at 1 dose level below the monotherapy RDE (RDE-1) with fixed doses of fulvestrant [REDACTED]. The definitions of MTD and RDE are provided in [Section 4.3.6](#) and [4.3.7](#). In addition, depending on the safety findings in Part 1A, and whether significant overlapping toxicities are expected in combination, the starting dose of PF-07248144 in combination can be further modified to a lower dose. The sponsor may choose to advance a lower dose to start the combination dose finding Part 1B, [REDACTED] prior to the monotherapy MTD being reached. This decision will be made based on emerging preliminary safety, PK, PD, and/or activity data during Part 1A. At least 2 DLT evaluable participants will be required for dose level groups in Part 1B, [REDACTED].

After the determination of the monotherapy expansion RDE in Part 1A, PF-07248144 will be evaluated in a dose expansion cohort as a monotherapy in locally advanced or metastatic ER+HER2- breast cancer (2L+) who have progressed after at least 1 prior line of CDK4/6 inhibitor and 1 line of endocrine therapy (Part 2A). The definitions of RDE and RP2D are provided in [Section 4.3.7](#). [REDACTED]

A food effect assessment will take place in a subset of participants (approximately 6) in Part 2A. Each participant will serve as his/her own control in which PF-07248144 will be

administered in the morning under “fed conditions” on Cycle 1 Day -7 and under “fasted” conditions on Cycle 1 Day 1. Additional details are provided in [Section 4.3.8](#).

PK and metabolite profiling in both urine and blood will be assessed in a subset of participants (approximately 6) in Part 2A. Both urine and blood samples should be collected from the same participants at screening and on Cycle 1 Day 15 ([Sections 8.5.2](#) and [8.5.3](#)).

After determination of the combination RDE from Part 1B, PF-07248144 in combination with fulvestrant will be evaluated in a dose-expansion combination cohort in participants with advanced or metastatic 2-4L ER+HER2- breast cancer whose disease has progressed after at least 1 prior line of a CDK4/6 inhibitor and at least 1 prior line of endocrine therapy and who must not have received more than 3 lines of systemic therapies in advanced or metastatic setting (Part 2B). Paired [REDACTED]  
[REDACTED]

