#### 4.3.5. Dose Limiting Toxicity Definition

DLT evaluable: A participant is classified as DLT evaluable if the participant experiences a DLT or if the participant otherwise in the absence of a DLT receives at least 75% of the planned doses of PF-07248144 and has received all scheduled safety assessments during the

DLT observation period. If a participant fails to meet these criteria, the participant is classified as not DLT-evaluable and may be replaced.

DLT observation period: For the purpose of dose escalation, the DLT observation period for monotherapy dose escalation (Part 1A) and combination dose escalation (Part 1B, [REDACTED]) will be the first cycle of treatment (within 28 days of the first dose) with inclusion of the Cycle 2 Day 1 (Day 29) laboratory assessments in each participant.

Significant AEs considered to be related to the study intervention or treatment under investigation that occur after the DLT observation period will be reviewed in the context of all safety data available. That review may result in re-evaluation of the dosing level or regimen.

Severity of AEs will be graded according to CTCAE version 5.0. For the purpose of dose escalation/finding, any of the following AEs occurring in the first cycle of treatment (28 days) which are attributable to one, the other, or all agents in the combination will be classified as DLTs:

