#### **6.4. Study Intervention Compliance**

Participant compliance with investigational product will be assessed at each visit. Compliance will be assessed by direct questioning, counting returned tablets or capsules, and review of the participant diary. Deviation(s) from the prescribed dosage regimen should be recorded in the CRF with >80% of missed doses considered a protocol deviation.

All study intervention will be distributed to the participant by the appropriately designated study staff at the investigational site.

A diary will be provided to the participants to aid in compliance with the dosing instructions. The diary will be maintained by the participant to include missed or changed investigational product doses. Participants will be required to return all investigational product at every cycle and the number of investigational product remaining will be documented and recorded. The participant diary may also be used to support this part of the accountability process via a discussion between the study site staff and the participant. Discrepancies will be documented on the appropriate eCRF.

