### 9.3. Analysis Sets

1. Full analysis set.

The full analysis set includes all enrolled participants.

2. Safety analysis set.

The safety analysis set includes all enrolled participants who receive at least 1 dose of study intervention. Unless otherwise specified the safety analysis set will be the default analysis set used for all analyses.

3. Per protocol analysis set (evaluable for MTD).

The per protocol analysis set includes all enrolled participants who had at least 1 dose of study treatment and either experienced DLT or do not have major treatment deviations during the DLT observation period.

4. mITT Population.

The mITT is the analysis population that will follow the ITT principle and include participants receiving at least 1 dose of study medication with baseline assessment and at least 1 post baseline assessment, disease progression, or death before the first tumor assessment. The mITT population may be used for interim analysis and conference presentations when the study is still ongoing.

5. PK analysis sets.

The PK parameter analysis population is defined as all enrolled participants treated who do not have protocol deviations influencing PK assessment, and have sufficient information to estimate at least 1 of the PK parameters of interest.

The PK concentration population is defined as all enrolled participants who are treated and have at least 1 analyte concentration.

6. Response Evaluable Set.

The response evaluable population will include all participants who received at least 1 dose of study treatment and had baseline disease assessment and at least 1 post baseline disease assessment.

7. PD/Biomarker analysis set(s).

The PD/Biomarker analysis population is defined as all enrolled participants with at least 1 of the PD/Biomarkers evaluated at pre and/or post dose.

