### 9.4.1. Maximum Tolerated Dose Determination

Determination of MTD will be performed using a Per protocol analysis set (evaluable for MTD).

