| Per protocol analysis set (evaluable for MTD) | The per protocol analysis set includes all enrolled participants who had at least 1 dose of study treatment and either experienced DLT or do not have major treatment deviations during the DLT observation period.                                                                                                                                                                                                                       |
| mITT Population                               | The mITT is the analysis population that will follow the ITT principle and include participants receiving at least 1 dose of study medication with baseline assessment and at least 1 post baseline assessment, discontinuing due to disease progression, death or any other reason before the first tumor assessment. The mITT population may be used for interim analysis and conference presentations when the study is still ongoing. |
| PK analysis sets                              | The PK parameter analysis population is defined as all enrolled participants treated who do not have protocol deviations influencing PK assessment, and have sufficient information to estimate at least 1 of the PK parameters of interest.
The PK concentration population is defined as all enrolled participants who are treated and have at least 1 analyte concentration.                                                 |
| Response Evaluable Set                        | The response evaluable population will include all participants who received at least 1 dose of study treatment and had baseline disease assessment and at least 1 post baseline disease assessment.                                                                                                                                                                                                                                      |
| PD/Biomarker analysis set(s)                  | The PD/Biomarker analysis population is defined as all enrolled participants with at least 1 of the PD/Biomarkers evaluated at pre and/or post dose.                                                                                                                                                                                                                                                                                      |

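### Section 6.4 sets the missed-dose deviation threshold the wrong way round, and Section 9.3 defines the MTD set without the DLT-evaluable criteria of Section 4.3.5

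*Protocol*

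**What the plan says.** Section 6.4 (Study Intervention Compliance) gives the only numerical missed-dose deviation threshold in the readable text: "Deviation(s) from the prescribed dosage regimen should be recorded in the CRF with >80% of missed doses considered a protocol deviation".

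Section 4.3.5 says who is DLT-evaluable. A participant qualifies by having a DLT or, without one, if he or she "receives at least 75% of the planned doses of PF-07248144 and has received all scheduled safety assessments" in the observation period. Otherwise "the participant is classified as not DLT-evaluable and may be replaced".

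The cohort minimums in Section 4.1 count participants on that basis: "at least 2 DLT evaluable participants per dose level group in the remaining cohorts for Part 1A", and "At least 2 DLT evaluable participants will be required for dose level groups in Part 1B".

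Section 9.4.1 then says: "Determination of MTD will be performed using a Per protocol analysis set (evaluable for MTD"). Section 9.3 defines that set differently, as participants with at least one dose who "either experienced DLT or do not have major treatment deviations during the DLT observation period". Section 3 of the SAP uses the same wording: "who had at least 1 dose of study treatment and either experienced DLT or do not have major treatment deviations". Neither place cites Section 4.3.5 or says what makes a treatment deviation major.

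**The concern.** There are two separate faults of wording.

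First, a rule under which a participant may miss most of a cycle without a protocol deviation cannot be squared with a 75% dosing minimum elsewhere in the same protocol. Doses are still recorded, so what fails is the classification of substantial under-dosing.

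Second, evaluability for the MTD has two stated criteria, and the MTD analysis uses the looser one. Section 4.3.5 asks for adequate dosing and complete safety assessment. Section 9.3 asks only that there be no major treatment deviation. A DLT-free participant who was under-dosed or incompletely observed can enter the denominator, and the cohort minimums and the MTD can rest on different participants. In a dose escalation that error leans towards accepting a dose.

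**Working it through.** The plan gives no figure of its own to reproduce here, so the check compares the rules.

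**1. Doses.** PF-07248144 is given once daily without a break (Section 6.1.1.1) and the DLT period is 28 days (Section 4.3.5), so 28 doses are planned. Section 6.4 names no period; one cycle is assumed.

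- 6.4 as written: missed/28 > 0.80. Since 0.80 × 28 = 22.4, a deviation needs at least 23 missed (at most 5 taken).
- 4.3.5: taken/28 ≥ 0.75. Since 0.75 × 28 = 21, at most 7 may be missed.
- Not DLT-evaluable, yet no deviation: 8 to 22 missed, which is 20 down to 6 taken (20/28 = 71% to 6/28 = 21%).
- Inferred intent, a deviation below 80% taken: 22 or fewer taken, so 6 or more missed. Today 6 to 22 missed go unflagged. Under this rule 21 or 22 taken (75% to 79%) would be a deviation but still evaluable.
- A 75% threshold: a deviation from 8 missed, matching 4.3.5 exactly.

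**2. Cases that fail 4.3.5 without clearly failing 9.3.**

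- A missed safety assessment. It is not a treatment deviation, however major is defined.
- A hold the protocol itself directs. Section 10.13.3.4 recommends at least 14 days for symptomatic SARS-CoV2 infection. If 14 days fall within Cycle 1, at most 28 − 14 = 14 doses are taken (50%).
- A toxicity interruption under Section 6.6.1. Section 4.3.5 makes a delay an automatic DLT only beyond 2 weeks. A hold of 8 to 14 days leaves 20 to 14 doses (71% to 50%).
- Doses missed for reasons other than toxicity, if not judged major.

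**3. Observed rates.** Section 2.2.4 reports one DLT in each of three escalation groups. Suppose, purely for illustration, that one DLT-free participant in each was not evaluable:

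- 2 mg: 1/4 = 25% becomes 1/3 = 33%.
- 5 mg plus fulvestrant: 1/4 = 25% becomes 1/3 = 33%.
- 8 mg: 1/7 = 14% becomes 1/6 = 17%.

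**4. Effect through a dose-toxicity model.** The trial's prior is redacted, so this is illustration only. The model was logit p = log a + exp(log b) × log(d/dref), with log a ~ N(m, sa²) and log b ~ N(0, sb²). The settings were sa = 1, 1.5, 2; sb = 0.5, 1; dref = 8, 15 mg. For each, m was solved so that the prior chance of a DLT rate above 0.33 at 8 mg equals the 10.1% in Section 9.4.1. There were 400,000 draws.

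- Accrued Part 1A data, all treated counted (2 mg 1/4, 5 mg 0/4, 8 mg 1/7, 15 mg 0/6): chance of overdosing at 8 mg 0.002 to 0.004. With 1/6 at 8 mg: 0.003 to 0.005.
- A first cohort alone at 8 mg: 1 DLT in 2 evaluable gives 0.204 to 0.336. Counting one non-evaluable participant (1 in 3) gives 0.147 to 0.220. The first range straddles the 25% overdose limit of Section 9.4.1; the second lies wholly below it.

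**5. Escalation still to come.** Section 9.2.1 plans about 70 in Part 1, with 25 to 30 in Part 1A and 6 to 9 in Part 1B. Outside those parts that leaves 70 − 30 − 9 = 31 to 70 − 25 − 6 = 39. The 66 treated by 12 September 2022 are all in Parts 1A, 1B, 2A and 2B (21 + 4 + 33 + 8 = 66), so none of these places had been used. Amendment 4 adds a triplet dose escalation.

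**The case against.** The strongest reply is that Section 4.3.5 is plainly meant to govern. The set is labelled as evaluable for MTD, and 4.3.5 is the only operational definition of evaluability. Section 9.6 mentions participants to whom DLT assessment does not apply. SAP Section 4.5 allows replacement of participants who drop out because of COVID-19 without meeting the DLT criteria, and SAP Section 5.7.3 refers to a compliance calculation for the DLT period. What counts as a major deviation is often left to the SAP. All this makes it likely that the team applies 4.3.5. It does not remove the conflict between two stated criteria: the SAP repeats the 9.3 wording, and no definition of a treatment deviation naturally covers a missed safety assessment.

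Much under-dosing caused by toxicity is already counted as an event. Under 4.3.5, a toxicity delay of more than 2 weeks and a treatment-related dose reduction in the first 28 days are DLTs. This stands and narrows the gap to the cases in step 2 of the working.

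For 6.4, the CRF still captures deviations from the regimen, tablet counts and diaries continue, and no analysis set cites the 80% figure. This also stands: the fault is in classification.

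A reader might infer that the 6.4 threshold feeds the MTD set, so that only 23 or more missed doses would exclude anyone. The documents do not link the two sections. A reader might also infer that counting a non-evaluable participant always understates toxicity. That is too strong: a fully dosed participant who misses one assessment is misclassified only if that assessment would have shown a DLT.

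**Conclusion.** Both wordings should be corrected. Section 6.4 is wrong as written; that 80% compliance was intended is an inference, because the protocol does not give the intended figure. Section 9.3 does not carry the 4.3.5 criteria into the set on which the MTD is determined.

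The size is modest. The shift from 25% to 33% is hypothetical, the model effect on the accrued Part 1A data is negligible, and the first-cohort figures rest on assumed priors and on an 8 mg cohort already past. They show only how sensitive a very small cohort can be; the effect in the trial's own model cannot be computed.

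Two stronger readings are tempting and unsupported. One is that the 5 mg recommended dose for expansion is in doubt: nothing shows that any counted participant was non-evaluable. The other is that about 45 escalation places remain (70 − 25 treated). That counts unused Part 1A and 1B places, although Section 2.2.4 reports the recommended dose already identified for both regimens. The relevant range is 31 to 39.

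**What to change.** - In Section 6.4, state that taking less than 80% of planned doses (more than 20% missed) is a protocol deviation, and name the period. Alternatively use less than 75%, which matches 4.3.5.
- In Section 9.3, and in SAP Section 3, define the evaluable-for-MTD set as participants who meet the 4.3.5 DLT-evaluable criteria: a DLT, or at least 75% of planned PF-07248144 doses together with all scheduled safety assessments.
- If 80% is kept in 6.4, add that such a deviation alone (75% to 79% of doses taken) does not remove a participant from the MTD set.

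The cost is two wording edits and at most one added sentence. A participant who falls out of the set may be replaced, as 4.3.5 already allows, so the design does not change.

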#### **6.5. Concomitant Therapy**

Concomitant treatment considered necessary for the participant's well-being may be given at the discretion of the treating physician.

All concomitant treatments, blood products, as well as nondrug interventions (*eg, paracentesis*) received by participants from screening until the EOT visit will be recorded on the CRF.

##### **6.5.1.**

[REDACTED]

#### 6.5.2. Fulvestrant [REDACTED]

Please refer to the [REDACTED] product labels of fulvestrant, [REDACTED] for a list of prohibited concomitant medications.

[REDACTED]

[REDACTED]

[REDACTED]

[REDACTED]

[REDACTED]

[REDACTED]

[REDACTED]

### **6.5.3. Other Antitumor/Anticancer or Experimental Drugs**

No additional anti-tumor treatment will be permitted while participants are receiving study treatment. Additionally, the concurrent use of vitamins or herbal supplements is not permitted.

[REDACTED]

### **6.5.4. Supportive Care**

Palliative and supportive care for disease related symptoms may be administered at the investigator's discretion and according to the specific supportive care product Prescribing Information or the current ASCO guidelines.

### **6.5.5. Hematopoietic Growth Factors**

Primary prophylactic use of CSF is not permitted during the first 28 days of Cycle 1 Part 1, but they may be used to treat treatment-emergent neutropenia as indicated by the current ASCO guidelines. During the screening window (ie, 28 days prior to Day 1), G-CSF compounds are not permitted to qualify a participant with low WBC counts. For Japan only: since the indication and dosage of G-CSF compounds approved in Japan may differ from ASCO guidelines, please refer to Japanese package insert.

Erythropoietin may be used at the investigator's discretion for the supportive treatment of anemia. (Note: erythropoietin is not approved for anemia caused by chemotherapy in all local regions that includes being not approved in Japan).

#### **6.5.6. Anti-Diarrheal, Anti-Emetic Therapy**

Primary prophylactic use of anti-diarrheal and anti-emetic therapy beyond the first cycle is at the investigator's discretion. The choice of the prophylactic drug as well as the duration of treatment is up to the investigator with sponsor approval assuming there is no known or expected drug interaction and assuming the drug is not included in the [Concomitant Therapy](#) section.

#### **6.5.7. Anti-inflammatory Therapy**

Anti-inflammatory or narcotic analgesic may be offered as needed assuming there is no known or expected drug-drug interaction and assuming the drug is not included in the [Concomitant Therapy](#) section.

#### **6.5.8. Corticosteroids**

Chronic systemic corticosteroid use (prednisone >10 mg/day or equivalents) for palliative or supportive purposes is not permitted. However, corticosteroid use for a short duration (eg, ≤10 mg/day of prednisone, for 2 weeks) as symptomatic treatment on an individual basis may be considered after discussion with sponsor's medical monitor or designee. For adrenal insufficiency replacement therapy, doses <15 mg/day of prednisone or equivalent will be allowed. Acute emergency administration, topical applications, inhaled sprays, eye drops, or local injections of corticosteroids are allowed.

